## 474 6.5 Efficacy Assessments

475 Screening assessments must include magnetic resonance imaging (MRI) with gadoxetate  
476 disodium as well as dual-tracer PET-CT with contrast enhanced triphasic CT scan of the liver  
477 for tumor contouring and treatment planning for SBRT.

478 Follow-up imaging with MRI with gadoxetate disodium injection and dual-tracer PET-CT  
479 scan with contrast-enhanced triphasic CT scans every 3 months after SBRT will be arranged  
480 for treatment response evaluation by RECIST 1.1, mRECIST, and PERCIST  
481 (APPENDIX 4 and APPENDIX 5) and surveillance for recurrence/relapse.

482 At the investigator's discretion, scans should be repeated at any time if progressive disease is  
483 suspected.

484 Confirmation of progression guidelines are set for the following reasons:

- 485 • for patient management and treatment decisions
- 486 • when scans are evaluated by two independent radiologists.

Confirmed objective disease progression refers to either of the following scenarios: 1. clinical progression/deterioration followed by a radiologic verification scan (progressive disease [PD] by RECIST 1.1, mRECIST, and PERCIST); or 2. in the absence of significant clinical deterioration, radiologic PD by RECIST 1.1, mRECIST, and PERCIST followed by a second radiologic confirmation scan with PD assessed according to the specific confirmation of progression criteria listed below. The confirmatory scan should occur preferably at the next scheduled imaging visit and no earlier than 4 weeks following the date of the immediate prior assessment of PD.

Immediate prior radiologic progression would be considered confirmed if any the following criteria are met in the confirmatory scan:

- $\geq 20\%$  increase in the sum diameters of target lesions (TLs) compared with the nadir at 2 consecutive visits, with an absolute increase of at least 5 mm in sum of diameters compared to nadir,

- and/or significant progression (worsening) of non-target lesions (NTLs) and/or of pre-existing new lesions at the confirmatory scan time-point compared with the immediate prior time-point (Note: Pre-existing new lesions are evaluated as NTLs at the confirmatory scan time-point),

- and/or additional new unequivocal lesions at the confirmatory scan time-point.

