## **8.1 Analysis Endpoints**

### **8.1.1 Efficacy Endpoint**

#### **Primary**

- Progression-free survival (PFS)
  - PFS is calculated from the start of SBRT to the date of radiologically confirmed progressive disease based on RECIST 1.1, mRECIST, and PERCIST, or death from any cause
- Best objective response as defined by RECIST 1.1, mRECIST, and PERCIST

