**APPENDIX 2. Scanning algorithm of magnetic resonance imaging (MRI) scan with gadoxetate disodium injection**

MRI scanning was conducted with a 3-Tesla MR scanner (Philips Achieva 3.0T TX, Philips Medical Systems, Best, The Netherlands) throughout the whole study as shown below. The same scanner is used for all scans for all patients recruited into this study. MRI scans were performed at baseline, then at every 3 months until liver transplantation was performed or progressive disease was observed, whichever came earlier. All HCC lesions were evaluated by two independent radiologists and any discrepancy in determining the nature of the lesions was solved by consensus.

(1) T2-weighted TSE single-shot in 5mm section thickness

(2) Breath-hold triggered T1-weighted in-phase and opposed sequences in 7mm section thickness

(3) T2-weighted SPAIR with TE 80 and 160 in 7mm section thickness

(4) Diffusion-weighted single-shot echo planar imaging with respiratory triggering

(5) Gadoxetate disodium (0.025mmol/kg body weight)-enhanced dynamic phases: unenhanced, late arterial-phase, portal-venous phase, and delayed phases with T1-weighted three-dimensional (3D) turbo-field-echo sequence (T1 high-resolution isotropic volume examination, THRIVE) with a 2-mm section thickness and a FOV of 32-38 cm.

1038

1039 **APPENDIX 3. Positron-emission tomography with integrated contrast-enhanced computed**  
1040 **tomography (PET-CT) with two radiotracers (C-acetate [ACC] and F-**  
1041 **fluorodeoxyglucose [FDG])**

1042 Dual Tracer PET-CT scan was performed at baseline, and then every 3 months after SBRT  
1043 until liver transplantation done or until progressive disease whichever came earlier. All scans  
1044 were performed using the same scanner and protocol (Discovery VCT, 64-MDCT; GE  
1045 Healthcare Bio-Sciences Corp., Piscataway, New Jersey, USA). All patients are required to fast  
1046 for  $\geq 6$  hours, and the blood glucose concentration is  $\leq 8$  mmol/L before radiopharmaceutical  
1047 injection. ACC (440–590 MBq; 8.0 MBq/kg of body weight) was then administered  
1048 intravenously, and limited upper abdomen coverage acquired at 1 minute followed by a whole  
1049 body imaging is performed at 11 minutes after injection. Data acquisition with an integrated in-  
1050 line PET-CT scanner (Discovery VCT, 64-multislice CT; GE Healthcare Bio-Sciences Corp, NJ)  

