| PD – An increase of at least 20% in the sum of the diameters of target lesions, taking as reference the smallest sum of the diameters of target lesions recorded since treatment started | PD – An increase of at least 20% in the sum of the diameters of viable (enhancing) target lesions, taking as reference the smallest sum of the diameters of viable (enhancing) target lesions recorded since treatment started |

CR, complete response; PD, progressive disease; PR, partial response; SD, stable disease.

1097

1098

1099 **APPENDIX 5. PERCIST 1.0**

|                         | PERCIST 1.0                                                                                                                                                                                                                                                                                                                                                                                                                                                                                                                                                                                                                        |
|-------------------------|------------------------------------------------------------------------------------------------------------------------------------------------------------------------------------------------------------------------------------------------------------------------------------------------------------------------------------------------------------------------------------------------------------------------------------------------------------------------------------------------------------------------------------------------------------------------------------------------------------------------------------|
|                         | 
1. Measurable target lesion in hottest single tumor lesion SUL of “maximal 1.2 cm diameter volume ROI in tumor” (SUL peak). SUL peak is at least 1.5 fold greater than liver SUL mean + 2 SDs (in 3cm spherical ROI in normal right lobe of liver). If liver is abnormal, primary tumor should have uptake <math>> 2.0 \times</math> SUL mean of blood pool in 1cm diameter ROI in descending thoracic aorta extended over 2cm z-axis..
 
2. Tumor with maximal SUL peak is assessed after treatment. Although typically this is in same region of tumor as that with highest SUL peak at baseline, it need not be.
 |

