|                    | PMD – > 30% increase in ACC and/or FDG SUL peak, with > 0.8 SUL unit increase in tumor SUV peak from baseline scan in pattern typical of tumor and not of infection/treatment effect. OR: Visible increase in extent of ACC and/or FDG tumor                                                                                                                                                                                                                                                                                                                                                                                                                                                                                                                                               |

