|  | 
uptake (75% in TLA/TLG volume with no decline in SUL. OR: New ACC and/or FDG-avid lesions that are typical of cancer and not related to treatment effect or infection. PMD other than new visceral lesions should be confirmed on follow-up study within 1 month unless PMD also is clearly associated with progressive disease by RECIST 1.1. PMD should be reported to include percentage change in SUV peak, (ideally, time after treatment, in weeks) and whether new lesions are present/absent and their number (i.e., PMD, +35, 4, new: 5). Because SUL is continuous variable, dividing response criteria into limited number of somewhat arbitrary response categories loses much data. For this reason, PERCIST preserves percentage declines in SUV peak in each reported category. Because rapidity with which scan normalizes is important (faster appears better), PERCIST asks for time from start of treatment as part of reporting. For example, CMR 90, 1, is probably superior to CMR 90, 10, especially if latter patient were SMD20, 1. More than one measurement of PET response may be needed at differing times, and it may be treatment type-dependent. PERCIST 1.0 evaluates SUL peak of only hottest tumor. This is possible limitation of approach, but lesions and their responses are highly correlated in general. Additional data are required to determine how many lesions should be assessed over 1. A suggested option is to include the 5 hottest lesions, or the 5 observed on RECIST 1.1 that are most measurable. Percentage change in SUL can be reported for single lesion with largest increase in uptake or smallest decline in uptake. Additional studies will be needed to define how many lesions are optimal for assessment.
 |

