For PERCIST: Single-voxel SUL is commonly used but has been reported to be less reproducible than SUL peak, especially with very small single-voxel values. It is suggested, but not required, that lesions assessed on PERCIST be larger than the 1.5-cm-diameter volume ROI used to minimise partial-volume effects. Percentage changes are proposed to deal with SUL peak changes. Use of maximal SUL could be explored. If 5 lesions are used as exploratory approach, it is suggested that sum of SULs of baseline 5 lesions serve as baseline for study. After treatment, sum of same 5 lesions should be used. Percentage change in SUL is based on change in these sums from study 1 to study 2. Exploratory analysis can include calculating percentage change in SUL in individual lesions and averaging them. This may produce different result. We believe summed SUL approach will be less prone to minor errors in measurements. For total lesion glycolysis: Exploratory analysis can include either all foci of tumor with maximal SUL. 2SDs above normal liver, 5 lesions with highest SUL, or lesion with highest SUL. It is suggested that threshold approach, typically at 2 SDs above normal liver SUL, be used to generate lower bounds of ROI (3SDs could be used for very active tumors). We believe this approach will be less variable than methods based on maximal SUL with percentage of maximal cutoff. Criteria for progression include 75% growth in TLG/TLA for SUL and are conservatively placed at 75% increase. Because 20% increase in EORTC linear size scales to 73% volume increase, the figures are comparable. Progression is judged from best response if being assessed after first scan was performed. For response by TLG/TLA, we propose 45% reduction as useful starting point, but more data are needed to make firm recommendations. If TLG/TLA is determined, explicit methodologic details should be provided. It should not be a primary metric, but a secondary endpoint at this time.

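### PFS rests on confirmed progression, but the rules for ending imaging, for confirming progression and for the PERCIST reference scan conflict with one another

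*Protocol*

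**What the plan says.** **Endpoint.** Section 8.1.1 (Primary): "PFS is calculated from the start of SBRT to the date of radiologically confirmed progressive disease based on RECIST 1.1". The definition also names the other two response systems and counts deaths of any cause as events.

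**Confirmation (Section 6.5).** There are two routes. The first is clinical deterioration followed by one verification scan. The second, without significant deterioration, is radiologic progression followed by a second scan: "The confirmatory scan should occur preferably at the next scheduled imaging visit and no earlier than 4 weeks following the date" of the preceding assessment of progression. The second scan confirms if any of three criteria is met:
- a 20% or greater "increase in the sum diameters of target lesions (TLs) compared with the nadir at 2 consecutive visits"; the growth must also be 5 mm or more in absolute terms;
- significant worsening of non-target lesions or of new lesions already present;
- further unequivocal new lesions.

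If progression is not confirmed, assessments continue and the next progression again needs a confirmatory scan.

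**End of imaging.** Appendix 3 runs dual-tracer PET-CT "until liver transplantation done or until progressive disease whichever came earlier". Appendix 2 gives the same end for MRI, and the synopsis (Study Design) ends response imaging at transplantation or when progressive disease develops. None of the three says confirmed.

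**How progression is called.** Appendix 4, RECIST 1.1: "An increase of at least 20% in the sum of the diameters of target lesions, taking as reference the smallest sum of the diameters" since treatment started. The mRECIST column applies the same rule to viable, enhancing diameter. The Appendix 5 table calls metabolic progression on a rise of more than 30% in SUL peak, with more than a 0.8 "SUL unit increase in tumor SUV peak from baseline scan in pattern typical of tumor". Increased extent of uptake and new avid lesions are separate routes. A note to Appendix 5 adds: "Progression is judged from best response if being assessed after first scan was performed".

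**PERCIST confirmation (Appendix 5).** "PMD other than new visceral lesions should be confirmed on follow-up study within 1 month", unless RECIST 1.1 progression is also clear.

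**The concern.** The protocol defines confirmed progression only in Section 6.5, and three other places do not fit that definition. A site that follows the synopsis or Appendices 2 and 3 stops scanning at the point where Section 6.5 needs another scan. A reader who calls progression on SUL or on viable tumour is then given a confirmation test built on other measurements. Two readers of Appendix 5 can classify the same scan differently.

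These conflicts push mainly one way. A progression that is not confirmed, or not called until uptake passes its pre-treatment level, leaves PFS longer than it should be. In a single-arm trial there is no control arm in which the same error would cancel. An analysis plan can settle how an unconfirmed progression is counted, but it cannot recover a scan that was never acquired.

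**Working it through.** The protocol states no figure of its own on this point: it gives no assumed PFS, and its sample size rests on response rates. The check is therefore a comparison of passages, with arithmetic where thresholds differ.

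**1. End of imaging.** The second route in Section 6.5 needs a scan at least 28 days after first progression, and more scans if that one does not confirm. The synopsis and Appendices 2 and 3 end imaging at progression. Read as written, both instructions cannot be followed.

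**2. Confirmation against the criterion that called progression.**

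| Progression called by | Measured on | Matching confirmation criterion for a target lesion |
|---|---|---|
| RECIST 1.1 | total diameter | yes |
| mRECIST | viable (enhancing) diameter | only if the diameters are read as viable |
| PERCIST, SUL route | SUL peak | none |

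mRECIST illustration (assumed values): total diameter stays at 40 mm while the viable part grows from 10 to 16 mm.
- Viable change: (16 − 10)/10 = +60%, which is mRECIST progression.
- Confirmation on total diameter needs 1.2 × 40 = 48 mm, so 40 mm fails.
- Confirmation on viable diameter: +60% and +6 mm, which passes both the 20% and the 5 mm limits.

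**3. PERCIST reference scan (SUL route only).** Let B be baseline SUL peak, f the fractional fall and N = (1 − f)B the nadir.
- From baseline, progression needs SUL above 1.3B. The rise from nadir is 1.3B/N = 1.3/(1 − f). For f = 0.30 this is 1.3/0.70 = 1.86-fold.
- From best response, it needs SUL above 1.3N, a 1.3-fold rise.
- Both also need a rise above 0.8 SUL units over the reference. A 30% rise exceeds 0.8 only when the reference is above 0.8/0.3 = 2.67. Below that the 0.8 rule governs and the required fold-rise is larger. With f = 0.30, the 1.3-fold figure therefore applies when B is above 2.67/0.70 = 3.81.

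Illustration (assumed values): baseline 8, best 3, later 8.
- From baseline: 0% change; the threshold is 1.3 × 8 = 10.4, so this is not progression.
- From best response: (8 − 3)/3 = +167%; the threshold is 1.3 × 3 = 3.9, and the rise of 5 exceeds 0.8, so this is progression.

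**4. Confirmation window.** Section 6.5 allows day 28 or later. One month is 30 to 31 days. The shared window runs from day 28 to day 30 or 31, about two to three days. The visit that Section 6.5 prefers, three months on (365.25/4 ≈ 91 days), lies outside the Appendix 5 window.

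**The case against.** The strongest reply is that Section 6.5 is the operative text and already provides for scans after first progression. Its survival-only follow-up starts after confirmed progression, and it allows repeat scans at any time if progression is suspected. The stop wording sits in the synopsis and in two scanning appendices, where progressive disease could be taken to mean confirmed disease. That shows which way the conflict is best resolved. It does not remove it, because sites schedule scans from those passages.

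The best-response note can also be read as qualifying the table: baseline for the first assessment, best response afterwards. That reading is reasonable, but the note stands beside text on TLG and TLA, so its scope is unclear. The two windows do overlap, and the next visit is only preferred.

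Several stronger conclusions are tempting but not supported:
- *Confirmation is by size alone, or some progressions can never be confirmed.* Non-target worsening and additional new lesions also confirm, and after clinical deterioration one verification scan is enough.
- *Patients taken off imaging have no PFS event until death.* Section 6.5 continues assessment.
- *Most patients are affected because 85% are expected to respond.* The 85% is not tied to PERCIST, and only responders who later progress in uptake without other progression are affected.
- *Very large fold-rises after deep responses.* These ignore the note, the other metabolic routes and the 0.8-unit rule, which raises the best-response threshold as well.
- *Events are dated at the confirmatory scan.* No passage says so, and dating rules may sit in an analysis plan that is not shown.
- *Appendix 4 excludes new lesions as progression.* Its progression row does not list them, but Section 6.5 and Appendix 5 count them; the table is abbreviated.

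**Conclusion.** The concern holds as a set of internal conflicts in how a primary endpoint is ascertained. The end-of-imaging conflict is the most serious, because it decides whether the confirming scan exists. The missing criterion for uptake-only progression in a target lesion is a clear mismatch. The mRECIST mismatch depends on diameter meaning total diameter. The PERCIST reference and window are unclear enough that readers could apply them differently.

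The likely effect is longer PFS, through progressions that are not confirmed or are called late. This is a risk that depends on which passage is followed, not a certain result, and the number of patients affected cannot be derived from the protocol. The 1.86-fold against 1.3-fold contrast applies to the SUL route alone, after a 30% fall, where the 0.8-unit rule is not the binding one. The conclusion also assumes that each of the three response systems is meant to give its own progression call. The changes should be made, since they are small and protect a primary endpoint.

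**What to change.** 1. In the synopsis and Appendices 2 and 3, continue imaging until confirmed progression (or transplantation), as Section 6.5 already requires.
2. In Section 6.5, confirm progression on the criterion that called it: total diameter for RECIST 1.1, viable diameter for mRECIST, SUL for PERCIST. Keep the non-target and new-lesion criteria.
3. In Appendix 5, state in the table that progression after the first post-treatment scan is judged from best response, and that this covers SUL as well as TLG and TLA.
4. Reconcile the one-month window in Appendix 5 with the four-week minimum and preferred next visit in Section 6.5, keeping or removing the Appendix 5 exceptions explicitly.

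**Cost.** These are wording changes in the synopsis, Section 6.5 and Appendices 2, 3 and 5. The real consequence is that progression called by PERCIST alone needs a PET-CT as its confirmatory scan. Section 6.5 already schedules PET-CT every three months, so confirmation at the next visit adds no scan to that schedule; confirmation within one month would be off schedule. The synopsis names PET-CT only at baseline, 3 and 6 months, with CT every three months, so its schedule must be aligned too.

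### Without clinical deterioration, Section 6.5 has no criterion that confirms target-lesion progression by uptake (PERCIST), and it does not say that viable diameter counts for mRECIST, so PFS events may be late or lost

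*Protocol*

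**What the plan says.** Section 8.1.1 states: "PFS is calculated from the start of SBRT to the date of radiologically confirmed progressive disease based on" RECIST 1.1, mRECIST and PERCIST, or to death. Section 2.1 also joins the systems with 'and'; the Primary Objectives row of the synopsis uses 'or'.

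Section 6.5 gives two routes to confirmed progression.

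- **Route 1:** "clinical progression/deterioration followed by a radiologic verification scan", the scan showing PD by the named systems.
- **Route 2:** without significant clinical deterioration, radiologic PD "followed by a second radiologic confirmation scan with PD assessed according to the specific confirmation of progression criteria listed below".

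The list for route 2 has three entries, any of which suffices:

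- at least a 20% "increase in the sum diameters of target lesions (TLs) compared with the nadir at 2 consecutive visits", and at least 5 mm in absolute terms;
- "significant progression (worsening) of non-target lesions (NTLs) and/or of pre-existing new lesions at the confirmatory scan time-point";
- additional unequivocal new lesions.

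If PD is not confirmed, the patient continues to the next PD, which again needs confirmation. The investigator leaves the first PD reading unchanged.

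Appendix 4 defines mRECIST PD as "An increase of at least 20% in the sum of the diameters of viable (enhancing) target lesions" over the smallest such sum, with no absolute floor. Appendix 5 defines PERCIST progression (PMD) as more than a "30% increase in ACC and/or FDG SUL peak" together with a rise of more than 0.8 SUL units, or a visible increase in the extent of uptake, or new avid lesions. It adds its own rule: PMD other than new visceral lesions is confirmed on a follow-up study within 1 month, unless it is clearly also PD by RECIST 1.1.

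**The concern.** The endpoint names three systems, but the confirmation list for patients without deterioration is written in the terms of one. mRECIST and PERCIST are there to register viable or metabolically active tumour that size alone can miss. If progression by those systems must pass a size test to be confirmed, some of it will be recorded late or not at all. Scheduled imaging in patients who are otherwise well is where such findings would be expected, and that is route 2. At stake is the event definition of a co-primary endpoint in a trial whose title is about assessing response with dual-tracer PET-CT and gadoxetate MRI.

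**Working it through.** The protocol states no PFS rate or threshold, so there is no plan figure to reproduce. The 60% and 85% in Section 8 are objective response rates and do not enter here. The check is to apply the Section 6.5 list to lesions that are PD under the appendices.

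**Step 1. Definitions against the list (target lesions)**

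| System | What makes it PD | Matching entry in the Section 6.5 list |
|---|---|---|
| RECIST 1.1 (Appendix 4) | Sum of diameters up at least 20% from the smallest sum | Yes, with an added 5 mm floor |
| mRECIST (Appendix 4) | Sum of viable diameters up at least 20% from the smallest sum | Not named; covered only if the first entry is read as the viable sum |
| PERCIST (Appendix 5) | SUL peak up more than 30% and more than 0.8 units, or greater extent of uptake | None |

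**Step 2. A lesion that grows in viability and uptake but hardly in size** (assumed values)

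- Total diameter 36 mm at nadir, then 38 mm: 2/36 = +5.6%, +2 mm. Not RECIST 1.1 PD.
- Viable diameter 10 mm at nadir, then 20 mm: 10/10 = +100%. mRECIST PD.
- SUL peak 4.0 at baseline, then 5.5: 1.5/4.0 = +37.5%, and 1.5 exceeds 0.8. PMD.

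Suppose the second scan shows the same, with no non-target worsening and no additional new lesion. Read on total diameter, no entry is met. Read on viable diameter, the first entry is met (+100%, +10 mm). The mRECIST gap therefore depends on the reading. The PERCIST gap does not: a lesion that progresses in uptake alone meets no entry on either reading.

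**Step 3. The 5 mm floor**

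A 20% rise equals 5 mm when the nadir sum is 5/0.20 = 25 mm. Below 25 mm the floor is stricter than the percentage. Example (assumed): total 20 to 24 mm (+20%, +4 mm) and viable 10 to 14 mm (+40%, +4 mm). Both are PD as Appendix 4 states the criteria, and both fail the first entry on either reading. The floor therefore matters for mRECIST even if viable diameter is allowed.

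**Step 4. Direction**

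An unmatched confirmation test can only delay or remove events, so PFS moves upward. Appendices 2 and 3 end scheduled MRI and PET at transplantation. A lesion removed with the native liver can no longer grow in size, so an unconfirmed progression in that patient is lost rather than delayed.

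**Step 5. Illustration of size** (assumptions: exponential PFS, true median 12 months, a fraction f of first progressions of this kind, all lost)

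12-month PFS = exp(−ln 2 × (1 − f)).

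- f = 0: 0.500
- f = 0.10: exp(−0.624) = 0.536
- f = 0.40: exp(−0.416) = 0.660

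The formula counts every such event as lost. It also gives these patients only the remaining risk of a counted event afterwards, although viable regrowth would be expected to raise it. For given inputs it is therefore an upper bound, provided that these patients reach size growth, new lesions or death at least as fast as the others.

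**The case against.** A reader might infer that viability-only or uptake-only progression can never be confirmed and never becomes a PFS event. The documents do not support that.

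- Route 1 does not use the list.
- Appendix 5 has its own confirmation rule for PMD.
- Later size growth, a new lesion or death still gives an event.
- The first entry does not say total diameter. Under mRECIST it could be taken as the viable sum, and then the first lesion in the working is confirmed.
- Renewed uptake is not always PMD. Appendix 5 measures the SUL rise from the baseline scan, so a lesion whose uptake falls after SBRT and returns only to its baseline level does not qualify on that wording. The closing notes of Appendix 5 speak instead of judging from best response.

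The link to PFS can also be questioned. Section 8.1.1 does not cite Section 6.5. Section 6.5 gives its purposes as patient management and reading by two independent radiologists, and it keeps the first PD reading. If 'and' means that all three systems must show PD, viability-only regrowth already fails at the first scan, whatever the list says.

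These points limit the finding but do not remove it. Section 6.5 is the only general definition of confirmed progression in the protocol, and keeping a first reading does not make it confirmed. The favourable reading of the first entry is not stated and leaves PERCIST uncovered. The Appendix 5 rule sits badly with Section 6.5: a scan within 1 month and one not before 4 weeks overlap by at most about three days, and Section 6.5 prefers the next scheduled visit, which is 3 months on.

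It would also go too far to say that the trial cannot show what the imaging adds. Best objective response by each system is co-primary and does not pass through this list.

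**Conclusion.** The point holds in a limited form. In a patient without significant clinical deterioration, no criterion in Section 6.5 confirms target-lesion progression by uptake. The diameter criterion follows RECIST 1.1, with a 5 mm floor, and does not say that viable diameter counts for mRECIST. If the rule is followed as written and PFS uses it, such events are counted late, or lost when transplantation comes first, and PFS is biased upward.

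The size of the bias cannot be derived from the documents. The 54% to 66% against 50% rests on an assumed 12-month median and an assumed 10% to 40% share, and it is an upper bound under those inputs. No stated PFS decision would change, because the protocol sets no PFS threshold. The passages should still be settled before PFS is derived, because they define an event of a co-primary endpoint.

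**What to change.** For the PFS endpoint, state that each system is confirmed on its own measure:

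- **RECIST 1.1:** sum of target-lesion diameters, as now.
- **mRECIST:** sum of viable (enhancing) diameters against its own nadir, saying whether the 5 mm floor applies.
- **PERCIST:** PMD by SUL peak or by extent of uptake, met again on the follow-up PET.

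Keep the non-target and new-lesion criteria for all three. Reconcile three further pairs of statements:

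- the confirmation timing in Section 6.5 with that in Appendix 5;
- the baseline reference for PMD in Appendix 5 with the best-response reference in its closing notes;
- 'and' in Sections 2.1, 6.5 and 8.1.1 with 'or' in the synopsis, so that it is clear whether PD by one system is an event.

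Limit the change to the endpoint definition. Confirmed progression is also a reason for stopping study treatment in Section 5.2, and that use need not be touched.

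The cost is wording. Under the 3-monthly MRI and PET of Section 6.5 and Appendices 2 and 3, the measurements are already taken. The synopsis lists MRI and PET only to 6 months, with CT continuing, so the schedule has to be reconciled for this to hold throughout. The small downside is more or earlier confirmed events, so PFS looks slightly less favourable.
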